**Methods/design:**

An exploratory phase II non-pharmacological randomised controlled trial where patients including young children, adolescents and adults with juvenile idiopathic arthritis and associated foot/ankle problems will be randomised to receive integrated podiatric care via a new foot care programme, or to receive standard podiatry care. Sixty patients (30 in each arm) including children, adolescents and adults diagnosed with juvenile idiopathic arthritis who satisfy the inclusion and exclusion criteria will be recruited from 2 outpatient centres of paediatric and adult rheumatology respectively. Participants will be randomised by process of minimisation using the Minim software package. The primary outcome measure is the foot related impairment measured by the Juvenile Arthritis Disability Index questionnaire's impairment domain at 6 and 12 months, with secondary outcomes including disease activity score, foot deformity score, active/limited foot joint counts, spatio-temporal and plantar-pressure gait parameters, health related quality of life and semi-quantitative ultrasonography score for inflammatory foot lesions. The new foot care programme will comprise rapid assessment and investigation, targeted treatment, with detailed outcome assessment and follow-up at minimum intervals of 3 months. Data will be collected at baseline, 6 months and 12 months from baseline. Intention to treat data analysis will be conducted.

A full health economic evaluation will be conducted alongside the trial and will evaluate the cost effectiveness of the intervention. This will consider the cost per improvement in Juvenile Arthritis Disability Index, and cost per quality adjusted life year gained. In addition, a discrete choice experiment will elicit willingness to pay values and a cost benefit analysis will also be undertaken.

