### Sample size

The sample size for the study has been pre-determined by power analysis of the primary outcome measure; the impairment domain of the JAFI questionnaire (JAFI-IMP. Sixty patients (30 in each trial arm) will allow detection of a 1 point reduction in the JAFI-IMP score (a conservative assumption determined by the trial steering committee) at six months from baseline at a significance level of p < 0.05 and power of 90%. These figures take into account the estimated potential participant drop out rate over the first six months of the trial (8 patients in each trial arm). The exploratory nature of the trial will permit in-depth examination of the suitability of the JAFI as a primary outcome measure for use in definitive multi-centre trials.

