### Statistical analysis

The primary analysis will compare the JAFI scores for each dimension between the intervention and control group at six months from baseline. This is to be conducted using a two-sided t-test. Should the distribution of change scores be skewed, a Mann Whitney test may be used to analyse the primary outcome variable in preference to a t-test. The longitudinal JAFI scores, at 0, 6, and 12 months will be analysed using repeated measures ANOVA with post hoc testing to identify significant differences between treatment groups and time points.

Core outcome variables scores for each group will be compared using a confidence interval for the difference in proportions. This will be based on a normal approximation to the binomial distribution.

Changes in predetermined gait variables (see Patients assessments and outcome measures section) from baseline to 12 months from baseline will be investigated within each treatment group using a one-sample procedure (t test or Signed Ranks test) and compared across treatment groups using the equivalent two-sided procedure (t test or Mann-Whitney test).

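### The longitudinal JAFI ANOVA counts the pre-randomisation score as an outcome, names no arm contrast and, in its classical form, drops anyone missing one of three scores

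*Protocol article*

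**What the plan says.** The Statistical analysis section sets out two analyses of the JAFI.

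- **Primary, at six months:** "The primary analysis will compare the JAFI scores for each dimension between the intervention and control group at six months from baseline". The test is given as "This is to be conducted using a two-sided t-test", with a Mann-Whitney test as the alternative if change scores are skewed.
- **Longitudinal:** "The longitudinal JAFI scores, at 0, 6, and 12 months will be analysed using repeated measures ANOVA with post hoc testing". Its purpose is "to identify significant differences between treatment groups and time points". No model term is named as the treatment comparison.

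Other parts of the article bear on the second analysis:

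- The abstract gives the impairment domain at both 6 and 12 months as the primary outcome and promises: "Intention to treat data analysis will be conducted".
- Initial assessments and outcome measures has all baseline measurements taken before allocation. Randomisation lists the JAFI-IMP score as a minimisation factor, with age and gender.
- Sample size allows for the "estimated potential participant drop out rate over the first six months of the trial (8 patients in each trial arm"). It gives no figure for loss between 6 and 12 months.

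**The concern.** Two features of the longitudinal analysis look wrong.

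**Month 0 is used as an outcome.** Baseline is recorded before allocation and the arms are balanced on it by minimisation, so the expected arm difference there is zero. A group effect averaged over three visits includes a visit that cannot carry a treatment effect. The baseline score would do more good as a covariate, where it reduces residual variance.

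**Incomplete patients are lost.** Classical repeated measures ANOVA needs a full row of three scores. A patient who returns the six-month postal form but misses the 12-month visit drops out of the analysis, six-month score included. That is an analysis of completers, under a general promise of intention to treat.

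At stake is the 12-month comparison. The abstract makes it part of the primary outcome, and no other analysis in the Statistical analysis section addresses it for the JAFI.

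**Working it through.** **Inputs from the article.** 30 per arm; a 1-point JAFI-IMP difference; alpha 0.05, two-sided; power 90%; 8 of 30 lost per arm in the first six months; scores at 0, 6 and 12 months.

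**Assumptions, not in the article.** SD 1 at each visit; equal correlation ρ between visits, 0.5 with a range of 0.3 to 0.7; the same 1-point effect at 6 and 12 months; 22 complete patients per arm.

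**Step 1: the plan's own figure.** No SD is stated, so the sample size cannot be reproduced, only back-solved. For a two-sample t-test with 22 per arm, a 1-point difference and 90% power, the noncentral t distribution gives SD = 1.00 (normal approximation: 1.02). Allowing for loss, 22 / (1 − 8/30) = 30. The stated size is consistent with an SD of about 1, which is why that value is used below.

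**Step 2: arm main effect over three visits.**

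- Estimate: (0 + 1 + 1)/3 = 0.667 points.
- Variance of a patient's three-visit mean: (1 + 2ρ)/3 = (1 + 1)/3 = 0.667 at ρ = 0.5.
- Standardised effect: 0.667/√0.667 = 0.816.
- Power with 22 per arm (noncentral t): 75%.

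**Step 3: baseline-adjusted mean of the two follow-ups.**

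- Estimate: (1 + 1)/2 = 1.0 point.
- Residual variance: (1 + ρ)/2 − ρ² = 0.75 − 0.25 = 0.5.
- Standardised effect: 1/√0.5 = 1.414.
- Power with 22 per arm: 99.6%.

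**Step 4: arm-by-time interaction in the same ANOVA.**

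- Deviations of the effects 0, 1, 1 from their mean: −0.667, 0.333, 0.333; sum of squares 0.667.
- Noncentrality: (22/2) × 0.667/(1 − 0.5) = 14.67, on 2 and 84 degrees of freedom.
- Power: 93%.

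**Step 5: range over the assumed correlation (22 per arm).**

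| ρ | Arm main effect (0.667) | Arm-by-time F test | Baseline-adjusted mean (1.0) |
|---|---|---|---|
| 0.3 | 84% | 82% | 99% |
| 0.5 | 75% | 93% | 99.6% |
| 0.7 | 68% | 99.5% | over 99.9% |

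A normal approximation puts the main-effect column at 86%, 77% and 70%. The conclusion is the same.

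**Step 6: an unequal effect.** With effects 0, 1, 0.5 the main effect is 0.5, against a follow-up mean of 0.75. This is again one third lower, because one of the three visits contributes zero.

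**Step 7: patients retained.** If the planned loss occurs, at most 22 per arm (44 of 60) have all three scores, and 8/30 = 26.7% are lost. A patient who leaves before six months and does not return has a baseline score only, and a model of the follow-up scores cannot use that patient either. The two methods differ only for patients with exactly one follow-up score. For illustration, if 2 or 4 per arm return the six-month form but miss 12 months, the ANOVA keeps 20 or 18 per arm (33% or 40% lost), while a mixed model keeps 22. The 2 and 4 are assumptions.

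**The case against.** The strongest reply is that this is a further analysis in an exploratory trial. The six-month test is designated primary, the trial is sized on it, and it uses every returned six-month form whatever happens later. That stands: nothing here affects the six-month comparison.

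Several stronger readings are tempting, and the document does not support them.

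- **That the treatment effect as such is diluted by a third.** This is true only of the arm main effect. The article names no term. The usual treatment test in this design, arm-by-time, is not diluted, and nor are arm contrasts at 6 or 12 months. What remains is that a reader cannot tell which term will be reported.
- **That the planned 27% loss shows a breach of intention to treat.** That loss falls before six months. Patients who leave then and do not return are lost to the replacement model as well. Loss after six months is not stated.
- **That the 12-month result will be biased by differential loss.** One can build such a case. With 26–29% of controls leaving after month 6, mostly those scoring badly, and 27% of the intervention arm leaving at random, completers show about 0.68–0.78 points at 6 months and 0.84–0.89 at 12, against a true 1.0. Different contact schedules make unequal loss conceivable, since intervention patients return every 3 months. But the plan assumes equal loss in both arms, so this is a scenario and not a plan figure.
- **That the post hoc tests are unadjusted.** The article does not say so, and many post hoc procedures include an adjustment.

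It can also be said that row deletion is not written down and that missing-data handling belongs in a full analysis plan. That is partly right: deletion follows from the classical form of the named method. But the choice of ANOVA and the inclusion of month 0 are stated in the article, so they are open to comment.

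**Conclusion.** The point holds in limited form. The longitudinal analysis enters a pre-randomisation score as an outcome, leaves the arm contrast unnamed and, in its classical form, excludes patients with partial follow-up, despite the stated analysis principle. It is secondary to the six-month test, yet it carries the 12-month JAFI comparison.

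If the arm main effect is the term read, a 1-point effect is estimated as 0.67 points with about 75% power, against over 99% for the baseline-adjusted mean of both follow-ups. If the interaction is read, power is about 93% and nothing is diluted. All three figures assume SD 1, correlation 0.5, 22 per arm and an equal effect at both visits. Over correlations of 0.3 to 0.7 the main effect has 68% to 84% power and the baseline-adjusted mean about 99% or more. The number of patients retained by changing the method, and any bias avoided, cannot be sized from the document.

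**What to change.** Replace the repeated measures ANOVA with a likelihood-based mixed model for repeated measures.

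- **Outcome:** JAFI-IMP at 6 and 12 months only.
- **Patients:** everyone randomised with at least one follow-up score, in the arm allocated.
- **Terms:** arm, visit, arm-by-visit, baseline JAFI-IMP, and the other minimisation factors (age and gender).
- **Report:** the arm difference with a confidence interval at 6 months and at 12 months, in place of the post hoc tests. Keep the six-month test as the primary analysis unless the trial team decides otherwise.

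The cost is a change of analysis wording and a few extra model parameters in a small sample. The model also relies on missing follow-up scores being missing at random, and patients with no follow-up score remain outside it. That should be said openly when intention to treat is claimed.

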Medical treatments in JIA appear to be well driven by outcome as preliminary definitions for improvement, minimal disease activity, inactive disease and clinical remission have been developed using the core outcome variables. These provide physicians with realistic therapeutic objectives [28-30]. Without objective and specific measures of foot related impairments and disability it is unlikely that clinical improvements can be detected. Currently there are no such outcome measures used in the routine podiatric care of children with JIA despite the recent development and validation of a disease and foot specific outcome measure; the JAFI [31]. The administration of a simple clinical measure such as the JAFI questionnaire as an appendage to routine medical note taking could permit objective monitoring of patients over time. Furthermore, clinicians can use clinical outcome measures to set realistic therapeutic goals in order to gauge improvements in their patients' conditions following interventions.

To summarise, there is a paucity of evidence to support simple podiatry alone as a complex intervention for foot problems in JIA patients. However significant improvements in the delivery of overall foot care may lead to a substantial increase in the uptake of this service. Utilisation of standardised and validated outcomes, as well as employing imaging techniques and thorough gait analysis should allow accurate monitoring, evaluation and appropriate alteration of treatments to achieve maximum treatment efficacy.

The FiJIA (Foot in Juvenile Idiopathic Arthritis) group aim to conduct an exploratory non-pharmacological phase II [32] randomised controlled trial of a new podiatry led integrated foot care programme versus current standard care podiatry for JIA patients with foot problems. The primary aim of this study is to evaluate the clinical and cost effectiveness of standard care podiatry and a new integrated foot care programme in the management of foot problems in JIA patients. The secondary aim of the study will be to determine what the optimum timing for intervention is in these patients by comparing the outcomes of pre-determined groups at different stages of the disease (children, adolescents and adults).

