Power Doppler	Display of signal flow in the synovium	0- No flow
		
		1- Single vessel signals
		
		2- Confluent vessel signals in less that half of the synovium
		
		3- Vessel signals in more than half of the area

To objectively measure lower limb and foot function, spatiotemporal gait parameters (walking speed, double-support time and symmetry index) will be assessed using an instrumented walkway (GaitRITE, CIR systems, Clifton, NJ, USA). Plantar pressure and force distribution will be measured using a pressure platform (Emed NT, Novel GmbH, Munich, Germany) using standardised protocols as previously developed in adult rheumatoid arthritis and JIA research [27,39,40]. From the gait analysis, six key variables will be selected: peak pressure in the forefoot; contact area in the toes; contact area in the midfoot; transfer of centre of pressure through the foot, and the peak ground reaction force during the loading response and terminal stance phases. Walking speed (m/s), stride length (m), cadences (steps/min), cycle time (% gait cycle), and double support time will be selected as a core set of spatiotemporal gait parameters and compared against age/gender normative values [27,39].

Arthritis activity measures will be assessed using the Core Outcome Variables for JIA, a validated clinical assessment for disease activity which correlates with adult measures. JIA patients under 16 years will have the Core Outcome Variables recorded (consisting of the CHAQ questionnaire completed by the patient or parent, active and limited joints, and physician global assessment completed by the doctor in clinic). For adults with JIA these will be the physician global assessment, pain assessment, number of tender, swollen and deformed joints and duration of early morning stiffness and HAQ. These adult and paediatric measures are comparable. The Glasgow Enthesitis Score, a non-validated measure of enthesitis severity, will be recorded by the examining doctor in all patients.

A variety of secondary outcomes will be recorded at baseline and at the final study visit (12 months from baseline). The Childhood Health Assessment Questionnaire (CHAQ) and the Health Assessment Questionnaire (HAQ) will be used as measures of overall function/disability in children/adolescents and adults respectively [41,42], while the EQ5D will be employed to measure general HRQoL, and will be used specifically within the economic evaluation [43].

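### The core outcome variables are scores, ratings, counts and a duration, but the article compares them as a difference in proportions without naming any yes/no response

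*Protocol article*

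**What the plan says.** The Statistical analysis section gives two sentences to these variables: "Core outcome variables scores for each group will be compared using a confidence interval for the difference in proportions", and then "This will be based on a normal approximation to the binomial distribution".

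The section on initial assessments and outcome measures defines the variables. For patients under 16 the set is described as "consisting of the CHAQ questionnaire completed by the patient or parent, active and limited joints, and physician global assessment". For adults it is a physician global assessment, a pain assessment, and "number of tender, swollen and deformed joints and duration of early morning stiffness and HAQ". The article calls the adult and paediatric measures comparable.

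The Background remarks that "preliminary definitions for improvement, minimal disease activity, inactive disease and clinical remission have been developed using the core outcome variables". That is the only place where yes/no states built from these variables appear.

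For the gait variables, which are also quantitative, the Statistical analysis section takes changes from baseline to 12 months, "compared across treatment groups using the equivalent two-sided procedure (t test or Mann-Whitney test").

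**The concern.** A confidence interval for a difference in proportions, resting on the binomial distribution, can be computed only when each patient is classed as a success or a failure. The sentence applies it to scores, and nothing listed in the core set is a success or a failure. Whoever runs the analysis must therefore either replace the method or create a binary variable that the article does not describe.

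Two things are at stake. First, the abstract puts disease activity first among the secondary outcomes, and its stated analysis cannot be run on the stated data. Second, if the variables are cut into two categories to fit the method, the comparison loses precision in a trial that has little to spare.

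**Working it through.** **Step 1. Set the method beside the data.**

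| Core variable (outcome measures section) | Set | Type | Yes/no? |
|---|---|---|---|
| CHAQ | under 16 | questionnaire score | no |
| Active joints, limited joints | under 16 | counts | no |
| Physician global assessment | both | rating | no |
| Pain assessment | adults | rating | no |
| Tender, swollen, deformed joints | adults | counts | no |
| Early morning stiffness | adults | duration | no |
| HAQ | adults | questionnaire score | no |

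The article does not describe the scales of the physician global and pain assessments; I read them as ratings. The methods state no cut-off, responder rule or other route from these variables to a proportion. The mismatch is complete at this point and needs no arithmetic.

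**Step 2. Numbers available.** The Sample size section gives 30 per arm and allows for 8 losses per arm by six months: 30 − 8 = 22 per arm, 44 in total. No 12-month figure is given, although the secondary outcomes are recorded at baseline and 12 months. I use 22 and 30 per arm as a working range. The sample size was set for the JAFI impairment score, so there is no planned power for the core variables to reproduce.

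**Step 3. Information lost by dichotomising (illustration).** For a normal score split at the median, the asymptotic relative efficiency is 2/π = 0.637. Then 44 × 0.637 = 28.0, so 44 patients carry the information of about 28.

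In power terms, assume a shift of d standard deviations and two-sided alpha 0.05. On the original scale, power is Φ(d/√(2/n) − 1.96). With a split at the control median, the proportions are 0.5 and Φ(d). For d = 0.8 and n = 22:

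- original scale: 0.8/√(2/22) = 2.653, and Φ(2.653 − 1.96) = 0.76;
- split: proportions 0.500 and 0.788, standard error 0.144 under the null and 0.138 under the alternative, so Φ((0.288 − 1.96 × 0.144)/0.138) = 0.52 (unrounded inputs).

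| Shift (SD) | 22 per arm: scale / split | 30 per arm: scale / split |
|---|---|---|
| 0.5 | 0.38 / 0.25 | 0.49 / 0.32 |
| 0.8 | 0.76 / 0.52 | 0.87 / 0.65 |
| 1.0 | 0.91 / 0.69 | 0.97 / 0.82 |

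The shifts are assumptions, and the article does not propose a median split.

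**Step 4. The normal approximation, if a binary response were intended.** The interval is p̂₁ − p̂₂ ± 1.96 √(p̂₁(1−p̂₁)/n + p̂₂(1−p̂₂)/n). Its exact coverage is the sum, over all pairs of binomial outcomes, of the probability of those pairs whose interval contains the true difference. The proportions below are assumed.

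| True proportions | 22 per arm | 30 per arm |
|---|---|---|
| 50% v 50% | 94.6% | 94.8% |
| 30% v 50% | 93.8% | 93.8% |
| 20% v 40% | 93.3% | 94.0% |
| 5% v 20% | 92.0% | 93.9% |
| 5% v 10% | 87.4% | 93.0% |
| 5% v 5% | 98.5% | 97.2% |

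Coverage is close to nominal for mid-range proportions and becomes erratic near 0 or 1. At 22 per arm and 5% v 20%, Newcombe's interval covers 96.8%. It is not better everywhere: at 40% v 60% with 22 per arm it covers 93.6%, against 94.5% for the normal approximation.

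Steps 3 and 4 describe different situations. A median split puts proportions near one half, where the approximation works well, so the two losses should not be added together.

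**The case against.** The strongest defence is that a responder analysis was intended. The Background says that definitions of improvement, inactive disease and remission have been built from these very variables, and the reference to the binomial distribution suggests that a binary endpoint was in mind. On that reading the word for scores is loose and the criterion merely unnamed, which a condensed article may leave to the full protocol or analysis plan.

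Part of this stands. A responder endpoint may have been meant, and leaving its details to a longer document would be no fault in itself. But the Background remark concerns medical treatment in general and lists several definitions, and the methods adopt none of them. The sentence still names scores as the quantity compared. A later document could repair it only by changing that quantity.

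Three stronger readings are tempting, and the article does not support them:

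- **A cut-off chosen after the data are seen.** Nothing in the article says when a definition would be fixed, so this would be an inference.
- **Proportions computed in very small age strata, with badly wrong coverage.** The sentence compares the two arms and plans no age-stratified analysis of these variables. The article calls the child and adult measures comparable, and it sets no age quotas from which stratum sizes could be derived.
- **The normal approximation as a serious fault in its own right.** Step 4 shows that it is a minor point at 22 to 30 per arm unless the proportions are extreme.

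**Conclusion.** Wrong as written. The stated method requires binary data, the stated variables are not binary, and no section of the methods links the two. This conclusion rests on the article's text alone.

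The numerical consequences are illustrative. The 64% figure assumes a normal score split at its median. The power figures assume a pure shift between normal distributions. The coverage figures assume particular response rates, and 22 per arm is the six-month number. None of these is needed for the mismatch itself.

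Severity: should be fixed. This is a secondary outcome in an exploratory phase II trial, and the primary JAFI comparison and the sample size do not depend on it.

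**What to change.** Replace the two sentences on the core outcome variables.

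- Compare each variable on its own scale at 12 months between arms, adjusted for its baseline value. A t test or Mann-Whitney test on change, as already planned for gait, would also serve.
- Keep the variables that differ between the paediatric and adult sets separate.
- Report each between-arm difference with a 95% confidence interval.
- If a responder endpoint was intended, name the definition and the time point in advance and say how it applies to adults as well as children. Report it as supportive, with a score-based interval such as Newcombe's, because response rates near 0 or 1 cannot be ruled out.

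The cost is a change of wording. The same data are collected, and neither the sample size nor the visit schedule changes.

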## Methods/design

### Study design and setting

FiJIA is a secondary-care based pragmatic exploratory randomised controlled trial where children (under 10 years of age) adolescents (between 10 and 16 years of age) and adults (16 years of age and over) will receive either standard care podiatry or intervention via a new foot care programme. A summary design is given in figure 1. A full economic evaluation will also be conducted.

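### The planned between-arm test of 12-month gait change is valid but ignores baseline and age and so loses power; the within-arm tests beside it say nothing about the programme

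*Protocol article*

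**What the plan says.** Under Statistical analysis, changes in the predetermined gait variables "from baseline to 12 months from baseline will be investigated" "within each treatment group using a one-sample procedure (t test or Signed Ranks test"). The same sentence goes on to say that they are "compared across treatment groups using the equivalent two-sided procedure", naming the t test and the Mann-Whitney test. No covariates are mentioned, and neither of the two analyses is given priority.

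Three other places bear on this:

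- Study design and setting enrols "children (under 10 years of age) adolescents (between 10 and 16 years of age) and adults (16 years of age and over"). The share of each group is not stated.
- Initial assessments and outcome measures lists six pressure and force variables, among them contact areas and peak ground reaction forces. It also lists five spatiotemporal variables, described as a "core set of spatiotemporal gait parameters and compared against age/gender normative values".
- Randomisation minimises on age, gender and JAFI-IMP score.

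**The concern.** Two things are at stake.

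First, some of these variables, such as stride length, contact area and ground reaction force, plausibly change with body size over a year whatever the treatment. In patients who are still growing, zero is then not the value expected without the programme. A within-arm test against zero mixes treatment with growth, time and background medical care.

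Second, the between-arm test does answer the treatment question, but not efficiently. If children change by growth and adults do not, age explains part of the spread in the change scores. Minimisation makes the arms alike on age, so this spread contributes little to the difference between the arms. An unadjusted test still counts it in the standard error. The test then rejects too rarely when there is no effect and has less power when there is one. It also makes no use of the baseline gait value beyond subtracting it.

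**Working it through.** **Inputs.** The article gives no figure for the gait analysis, so there is none to reproduce. The Sample size section gives 30 per arm and an allowance of 8 dropouts per arm by six months, hence 30 − 8 = 22. Dropout to 12 months is not stated. Alpha is 0.05, two-sided. Assumptions, because the document gives no values: growth *g*, in SDs of change within an age group, is the same in both arms; a share *f* of patients is growing; the other patients have no growth.

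**Within-arm tests, no treatment effect.** Let p be the power of the one-sample t test (noncentral t, noncentrality g√n). The chance of significance in exactly one arm is 2p(1−p). With every patient growing:

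| g | n = 22: p | exactly one arm | n = 30: p | exactly one arm |
|---|---|---|---|---|
| 0 | 5% | 9.5% | 5% | 9.5% |
| 0.3 | 27% | 39% | 36% | 46% |
| 0.5 | 61% | 48% | 75% | 37% |
| 0.8 | 95% | 10% | 99% | 2% |
| 1.0 | 99% | 1% | >99% | 0.1% |

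With adults in the arms, at g = 0.5 and n = 22, simulation (20,000 runs) gives 31% and 44% if two thirds grow, and 10% and 18% if one third grow.

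**Between-arm test, effect of ignoring age.** Suppose that the arms are balanced on growing status. The difference in mean change then has variance 2/n (within-group SD = 1), but the t test estimates the variance of change as about v = 1 + f(1−f)g². So, to a normal approximation:

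- type I error = 2[1 − Φ(1.96√v)]
- power for a true effect of 1 SD = Φ(√(n/2) − 1.96√v)

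With f = 1/3 or 2/3, f(1−f) = 0.222. With n = 22, √(n/2) = 3.317.

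| g | v | 1.96√v | type I error | power |
|---|---|---|---|---|
| 0 | 1.000 | 1.960 | 0.050 | 91% |
| 0.5 | 1.056 | 2.014 | 0.044 | 90% |
| 1.0 | 1.222 | 2.167 | 0.030 | 87% |
| 1.5 | 1.500 | 2.400 | 0.016 | 82% |
| 2.0 | 1.889 | 2.694 | 0.007 | 73% |

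The 20,000-run simulation of mixed arms at n = 22 agrees: type I error 0.045 to 0.046 at g = 0.5 and 0.030 to 0.031 at g = 1.0. When all patients grow equally it stays at about 0.05. Growth therefore never inflates this test.

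**Baseline value.** With correlation ρ between the two visits and equal variances, change has variance 2σ²(1−ρ) and the ANCOVA residual has σ²(1−ρ²), a ratio of (1+ρ)/2. If ρ is 0.5 or 0.7 (assumed), ANCOVA needs 75% or 85% of the variance.

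**Both together.** A simulation of the unadjusted test against the ANCOVA, under assumed mixed-age growth, gave type I error of about 0.01 to 0.045 and power of 64% to 80% for the unadjusted test, against about 0.05 and 89% for the ANCOVA.

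**Cost in degrees of freedom.** With 44 patients the t test has 44 − 2 = 42. An ANCOVA with intercept, arm and four covariates has 44 − 6 = 38.

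**The case against.** The strongest reply is that the correct test is already planned, in the same sentence, and that gait is a secondary outcome in an exploratory trial. This stands. Common growth cancels between the arms, and age and gender are minimised.

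A reader might infer something stronger: that growth will produce significant changes, and that a result significant in one arm only will be taken as a programme effect. The documents do not support this. Nowhere do they say that efficacy will be concluded from one arm or from setting the arms' p-values side by side. The order of two clauses is not a testing hierarchy. How often a within-arm test would be significant depends on growth and age mix, neither of which is given. The two feared results also do not peak together: strong growth makes both arms significant, and the one-arm-only rate then falls to about 1% at 22 per arm.

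Nor can it be said that the tested changes are unscaled. The spatiotemporal set is to be "compared against age/gender normative values", and any scaling of the other variables may be left to the full protocol or the SAP. Regression to the mean is not a strong argument either, since eligibility rests on the site of arthritis and not on extreme gait values.

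Two smaller replies also stand. Replacing a within-arm test with a confidence interval is largely relabelling. The word two-sided, where two-sample is meant, is a clerical slip that the named tests resolve.

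One thing survives these replies: validity does not make the unadjusted test efficient. The trial collects the baseline value and all three minimisation factors, and the stated analysis uses none of the factors.

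**Conclusion.** The point holds in a limited form. The within-arm tests cannot inform on the programme in a sample that includes growing patients. The between-arm test is valid but conservative and less powerful than it need be.

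The loss is negligible if growth is small against the spread of change (v = 1.056 at 0.5 SD) and material if it is large (power 73% against 91% at 2 SD, from age alone). These figures rest on assumed growth, an assumed age mix, equal growth in the arms and good balance on age. Dropout would weaken that balance and with it the conservatism. This is an inexpensive improvement to a secondary outcome, not a threat to the trial's conclusions, and it does not touch the primary JAFI result.

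**What to change.** Make the between-arm comparison the sole gait inference: for each variable, an ANCOVA of the 12-month value on arm, baseline value, age, gender and baseline JAFI-IMP. Age is best entered in the form used for minimisation, or as the trial's own three age groups, because growth does not run in a straight line into adulthood. Report the change within each arm as description only, and say so. Replace two-sided by two-sample in the same sentence.

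The cost is a change of wording, slightly more analysis work and about four degrees of freedom (38 against 42 with 44 patients; one fewer if age enters as three groups). No new data are needed.
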